# **5 STUDY PROCEDURES**

**Duration of Study**

Each patient enrolled in this study will participate in study procedures across their inpatient rehabilitation length of stay commencing with providing informed consent and concluding with discharge from inpatient rehabilitation at BSWIR.

In order to enroll 128 eligible patients with SCI, an estimated 3 years will be necessary to complete all study related activities.

**Visit Windows**

Patients will be asked to complete testing at 2 time points: within one week of admission to inpatient rehabilitation and within one week of discharge from inpatient rehabilitation.

| **Table 6: Patient Timeline** | | | | |
| --- | --- | --- | --- | --- |
| Study Phase | Admission | Treatment (UC or RGT) Intervention | Discharge | Data Source |
| **Consent** | X |  |  |  |
| Demographics | X |  | X | Medical Record |
| **Outcome Testing** |  |  |  |  |
| *Aim 2* |  |  |  |  |
| Walking Score Index for Spinal Cord Injury (WISCI-II) | X |  | X | Medical Record |
| 10-meter walk test (10MWT) | X |  | X | Medical Record |
| Spinal Cord Independence Measure (SCIM) | X |  | X | Medical Record |
| Numeric Pain Rating Scale (NPRS) | X |  | X | Medical Record |
| Fatigue Severity Scale (FSS) | X |  | X | Study Specific |
| Penn Spasm Frequency Scale (PSFS) | X |  | X | Study Specific |
| Patient Health Questionnaire – 9 (PHQ-9) | X |  | X | Study Specific |
| General Anxiety Disorder – 7 (GAD – 7)  International SCI Quality of Life Basic Data Set  Qualitative Questionnaire | X  X |  | X  X  X | Study Specific  Study Specific  Study Specific |
| *Aim 3* |  |  |  |  |
| Heart Rate (HR) |  | X |  | Study Specific |
| Ratings of Perceived Exertion (RPE) |  | X |  | Study Specific |
| Number of steps |  | X |  | Study Specific |

**Screening**

During the screening for consent process, the study staff will utilize the Orientation log (O-LOG), a cognitive assessment tool, to identify the ability for normal orientation. If the patient receives a score of >25 out of 30, the patient will be deemed to have normal orientation necessary for independent consenting and will be cleared to consent.

**Informed Consent**

Consent will be obtained prior to beginning any study-specific intervention. Individuals identified as meeting the inclusion/exclusion criteria during the weekly SCI team rounding meeting will be approached. Research staff and research associates will explain the study and answer any patient questions for clarification. Prospective patients will be approached within the first 7 days of their admission to BSW Rehab and will have until the end of their 10^th^ day to consent to participate. If a patient is not initially appropriate for intervention due to medical reasons and later determined to appropriate during their stay, they may be approached to consent to participate. Research staff and research associates will be responsible for obtaining informed consent. Informed consent will be obtained in private setting, specifically in the patient’s room and with a caregiver, or witness to consenting process if necessary. Qualified patients will be informed about the study and will be given adequate time to decide whether he/she would like to participate in the study. Caregivers of minors will sign consent form and minors will be given an opportunity to assent to project. Patients will be informed that their participation is voluntary and that they can withdraw from the study at any time. Participants will also be encouraged to ask questions throughout their participation in the study.

**Randomization**

Participants meeting the inclusion and exclusion criteria will be approached, screened, consented, and enrolled into the study. After obtaining informed consent, participants will be randomized to either the experimental (RGT) or UC control group using cluster randomization based on specific injury characteristic for stratified block.

The heterogeneity of the population in terms of injury severity is a concern given that these factors are expected to be important to walking recovery. To account for this, patients will be assigned to RGT or UC using 1:1 stratified blocks. Stratification will be based on specific injury characteristics (incomplete tetraplegia and incomplete paraplegia), and within each strata randomization blocks of size 6 will be used to ensure equal distribution between groups.

[figure not shown]

**Study Intervention**

*Staff training*

Therapists will have completed training for delivering RGT with exoskeleton and BSWTT. In addition, the RGT and UC activities will be led by trained therapists who are experienced with treating individuals with SCI. All study staff will be trained on study procedures at the project launch meeting and subsequent support meetings.

*Setting*

All session will be held at Baylor Scott & White Institute of Rehabilitation, an inpatient rehabilitation facility. The location of the intervention activities allows for therapists to provide assistance and supervision at all times.

*Compliance Data Collection*

Participants randomized into the RGT and UC group will be given a Polar heart rate monitor and a pedometer to wear during the gait training sessions. Participants will be asked to return their heart rate monitor be synced to the study staff’s computers and the study staff can review their activity and heart rate reports. Passwords and data will be de-identified and stored in a separate password-protected file. Number of steps will be captured by the Esko device and pedometer for the RGT and UC care group, respectively. **Table 7** provides more detailed information about the devices used in the study.

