| ****Ratings of Perceived Exertion (RPE)*** | The Borg RPE is a 15-point scale with verbal descriptors to standardize perceived exertion across tasks and individuals. Participants will be asked to provide a self-reported intensity level on the Borg Rating of Perceived Exertion Scale^122^ during RGT and UC gait training sessions. A self-report of 12 to 14 on the RPE indicates moderate intensity. The Borg RPE scale has been shown to be a valid measure of exercise intensity with weighted mean validity coefficient of 0.62 for HR.^123^ | ICF domain = Body Structure & Function |
| ***Number of Steps*** | The Ekso device records several data points for each session including **number of steps**, “Up” time (the amount of time spent standing in the device), “Walk” time (the amount of time spent walking in the device), and device assistance scores. While all of these data values will be recorded to describe each RGT session and tracked to monitor progression of the RGT intervention, the number of steps per session will be utilized as an indicator of RGT session intensity.^42,91^ We will consult our Consumer Advocates for recommendations on incorporating device scores such as “Up” time and “Walk” time as additional measures of intensity.  Number of steps for the UC group will be collected via pedometer during each gait training session. The number of steps captured on the device will be recorded on the CRF after each gait training session. The watch will be reset before each use. | ICF domain = Activity |
| *Each of these measures are core and supplemental instruments of the SCI CDE as developed through the collaboration of the International Spinal Cord Society, the American Spinal Injury Association, and the National Institute of Neurological Disorders and Stroke CDE team, and referenced at http://www.commondataelements.ninds.nih.gov/SCI.aspx. | | |

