Hypothesis 3.1: *RGT will be of significantly greater intensity with participants (1) spending more minutes per session and total minutes (over all sessions) in moderate intensity exercise (40% to 60% range of heart rate reserve), (2) reporting higher mean RPE across all sessions, and (3) completing more steps during each session and total number of steps over all sessions compared to UC.*

Hypothesis 3.2: *Intensity will be significantly correlated to the primary outcome (WISCI-II) for the RGT and UC groups.*

Hypothesis 3.1 will be evaluated using similar methods as Aim 2. Moderate intensity minutes, average RPE, and steps will be evaluated using individual general or generalized linear models, as appropriate, to determine the association between RGT and UC and intensity. Each model will control for the patient characteristics listed in section B.1.i.D and total number of sessions. Additionally, to determine the relationship between session intensity and walking function (Hypothesis 3.2) correlation coefficients will be calculated between each intensity measure and WISCI-II at admission, discharge, and change score.

For both Aims 2 and 3 stratified subset analysis will be performed for tetraplegia and paraplegia to determine if RGT has a differing impact depending on injury classification.

**Missing Data:** If a patient misses an assessment, their data for that outcome will be treated as missing and *will not* be included in the statistical model. However, the data from the completed assessments for that patient *will* be included. Sensitivity analysis will be performed to assess the impact of missing data, by imputing a missing outcome measure using the overall average change score for the given outcome. The sensitivity analyses will be compared to the initial analysis to determine the impact of missingness on the results

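### In the step-count part of Hypothesis 3.1, the counting device is fully confounded with arm, so the planned test cannot tell a treatment difference from a device difference.

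*Protocol*

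**What the plan says.** Section 5 (Study Intervention, Compliance Data Collection) assigns a different step counter to each arm: "Number of steps will be captured by the Esko device and pedometer for the RGT and UC care group, respectively". Table 7 in Section 6 repeats the assignment. For RGT, the Ekso logs each session and "the number of steps per session will be utilized as an indicator of RGT session intensity". For the comparator, "Number of steps for the UC group will be collected via pedometer during each gait training session", and that count is written on the case report form.

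The same paragraph of Section 5 issues the pedometer more widely: "Participants randomized into the RGT and UC group will be given a Polar heart rate monitor and a pedometer to wear" during gait training. Nothing in the protocol says that a pedometer count from an RGT session is recorded or analysed.

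Section 9 (Aim 3 Analysis) makes the counts a between-arm superiority outcome, with RGT participants "completing more steps during each session and total number of steps over all sessions compared to UC". The method is: "Moderate intensity minutes, average RPE, and steps will be evaluated using individual general or generalized linear models, as appropriate". On adjustment it says: "Each model will control for the patient characteristics listed in section B.1.i.D and total number of sessions".

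**The concern.** A between-arm comparison can be read as a treatment effect only if the outcome is measured in the same way in both arms, or if the difference in measurement is known. Here neither holds. The two counters also work in different settings: one is built into a powered suit and logs its own steps, and the other is worn during body-weight-supported treadmill or overground walking.

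At stake is one of the three intensity measures in Hypothesis 3.1, and one to which the protocol gives weight: Section 2 names intensity as a critical ingredient of gait training and step counting as the recommended way to track it. A finding of more steps in RGT could be a device artefact. A finding of no difference could be a true excess that the devices conceal.

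**Working it through.** **1. Which instrument serves which arm.**

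| Aim 3 measure | RGT | UC |
| --- | --- | --- |
| Heart rate | Polar monitor | Polar monitor |
| RPE | Borg scale | Borg scale |
| Steps | Ekso | Pedometer |

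Steps are the only one of the three with a different instrument in each arm (Section 5 and Table 7).

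**2. Whether the model can separate device from arm.** Let A = 1 for RGT and 0 for UC, and let D = 1 for an Ekso count and 0 for a pedometer count. As planned, D = A for every participant. In a model with mean b0 + b1·A + b2·D + covariates, only b1 + b2 can be estimated. Adjusting for patient characteristics and number of sessions does not change this. The protocol describes no calibration, agreement check, common definition of a step or observed count that would supply b2 from elsewhere.

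**3. How large the effect could be.** The protocol states no step mean, standard deviation or device accuracy, so there is no figure of its own to reproduce. The following is an illustration on assumed values.

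Inputs from Section 9: 64 per arm, about 10% attrition and a 5% level. This gives 64 × 0.9 = 57.6 per arm. The protocol does not state sidedness, so a two-sided test is assumed.

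Assumed: equal true steps in both arms (scaled to mean 1); a coefficient of variation c of 0.5 or 0.8; a pedometer that misses a fraction u of UC steps relative to the Ekso; an unadjusted two-sample t-test.

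- Recorded RGT: mean 1, SD c.
- Recorded UC: mean 1 − u, SD c(1 − u).
- Apparent ratio RGT/UC = 1/(1 − u).
- Pooled SD s = √{[c² + c²(1 − u)²]/2}; standardised difference d = u/s.

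Worked case, u = 0.2 and c = 0.5: s = √[(0.25 + 0.16)/2] = 0.453; d = 0.2/0.453 = 0.44; chance of p < 0.05 is 0.65.

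| u | Ratio | d (c = 0.8) | P(significant) | d (c = 0.5) | P(significant) |
| --- | --- | --- | --- | --- | --- |
| 0 | 1.00 | 0 | 5% | 0 | 5% |
| 10% | 1.11 | 0.13 | 11% | 0.21 | 20% |
| 20% | 1.25 | 0.28 | 31% | 0.44 | 65% |
| 30% | 1.43 | 0.43 | 64% | 0.69 | 96% |

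With the full 64 per arm the chances are slightly higher. If the pedometer overcounts relative to the Ekso, the bias runs the other way and a true RGT excess is masked.

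**4. Whether Hypothesis 3.2 is affected.** That hypothesis concerns correlations of intensity with WISCI-II for the RGT and UC groups. Within one arm there is one counter, and multiplying all its counts by a constant (1 − u) leaves a correlation coefficient unchanged. The device difference matters there only if the arms are pooled or their coefficients are compared.

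**The case against.** The strongest counter-argument is that a common pedometer is not a common error. RGT steps are taken inside a suit with motors at the hips and knees; UC steps are taken on a supported treadmill or overground. If pedometer accuracy differs between those settings, the error still follows arm, and dropping the Ekso's own record could replace one bias with another. This stands. It is why the Ekso counts should be kept beside the pedometer counts rather than replaced by them, and why an agreement threshold must be set in advance.

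It can also be said that issuing pedometers to both arms may be loose drafting, since Table 7 mentions the pedometer only for UC. That is possible. If so, the fix costs more than a form field, but the confounding is the same.

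The scope is narrow: one of three Aim 3 measures, with the primary outcome untouched and Aim 3 labelled descriptive in Table 7. This limits the weight of the point. It does not remove it, because Section 9 plans a between-arm test of a directional hypothesis on these counts.

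A reader might infer more than the documents support in two ways. One is that the pedometer will undercount in slow or assisted walkers and so favour RGT: no passage gives its accuracy or wear position, and the direction is unknown. The other is that Hypothesis 3.2 is compromised as well: the protocol does not say that arms will be pooled, and within-arm correlations survive a proportional miscount.

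**Conclusion.** The point holds for the step component of Hypothesis 3.1 and no further. As planned, the between-arm step test estimates treatment and device together, and the planned data contain nothing to separate them. This follows from the assignment of counters alone and needs no assumption.

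The size does rest on assumptions. The 11% to 96% range for a false significant result shows what a 10% to 30% relative undercount would do at coefficients of variation of 0.8 to 0.5 in an unadjusted test. It is not evidence that such an undercount will occur in this trial. The comparisons of heart-rate minutes, RPE and WISCI-II are not affected. This should be corrected, but it does not threaten the primary result.

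**What to change.** 1. Record the pedometer count on the case report form for RGT sessions as well, and state in Section 5 and Table 7 that it is collected in both arms.
2. Run the between-arm step comparison on the pedometer in both arms, and show the Ekso-versus-pedometer comparison beside it.
3. Report paired Ekso-pedometer agreement within RGT sessions, with the agreement threshold fixed before any comparison is run. If the threshold is not met, or the two comparisons disagree, describe steps by arm and draw no between-arm conclusion on steps.
4. Keep the Ekso counts to describe RGT dose.
5. For Hypothesis 3.2, state that step correlations are calculated within arm.

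The cost is one extra field per RGT session, given that Section 5 already has both arms wearing a pedometer. A limitation remains and should be stated: pedometer error may still differ between exoskeleton and usual-care walking. The paired counts show it for RGT sessions only, so pedometer error in UC stays unmeasured.

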**Payment**

While we will not pay participants for taking part in study, participants in the UC group will be offered up to 8 sessions of robotic gait training sessions in outpatient rehabilitation for their time/effort to attend each of the sessions and completed assessments which are required for research purposes. Each intervention group will complete a total of 2 assessments.

# **6 STUDY MEASUREMENTS**

**Study Endpoints**

The following data will be collected through the medical record and patient interview at baseline assessment: age; age at injury; injury severity; gender; ethnicity; education level; pre-morbid history of mental illness; residence status; income; insurance type; vocation; and financial status. Level of impairment will be captured using the ASIA Impairment Scale (AIS) to determine injury severity after traumatic SCI by the physician at admission to BSW. The AIS is standard of care at BSW and will be extracted from the medical record. The following data will be collected through medical record and patient interview within one week of admission and discharge: *Gait speed via 10-Meter Walk Test, Spinal Cord Independence Measure (SCIM), Numerical Pain Rating Scale (NPRS), *Fatigue Severity Scale (FSS), Penn Spasm Frequency Scale (PSFS), Patient Health Questionnaire - 9 (PHQ-9), Life Satisfaction Questionnaire (LiSAT-9), Heart Rate (HR), Ratings of Perceived Exertion (RPE), and Number of Steps*. Primary and secondary outcomes for Aim 2 and dose parameters for Aim 3 are described in **Table 7.**

| **Table 7. Outcome Measures for Proposed Project and link to ICF** | | |
| --- | --- | --- |
| **Aim 2 Primary Outcome:** To examine the efficacy of RGT compared to usual care gait training (UC) | | |
| ****Walking Index for Spinal Cord Injury – II (WISCI-II)*** | Our primary outcome, the WISCI-II defines the physical limitation for gait secondary to impairment at the person level and indicates the ability of a person to walk after SCI.^103^ Intrarater and interrater reliability are excellent at 1.0 and 0.98 respectively.^104^ A change of one WISCI level can be considered clinically significant.^105^ | ICF domain = Activity |
| **Aim 2 Secondary Outcomes** | | |
| ****Gait speed via 10-Meter Walk Test (10MWT)*** | Assesses gait speed over a short duration. Gait speed (m/s) is correlated ability to mobility in the community, capacity to perform activities of daily living, risk of falls, re-hospitalization, and risk of cognitive decline.^106^ We will assess gait speed at inpatient rehabilitation admit and discharge, 3- and 6-month follow-up sessions to monitor longitudinal changes throughout the study. For persons with SCI, a combination of the 10MWT and the WISCI-II is recommended to provide the most valid measure of improvement in gait.^107^ A change of >0.06 m/s is considered to exceed minimally clinically important difference (MCID)^108^ and test-retest reliability is excellent (ICC=0.97).^109^ | ICF domain = Activity |
| ****Spinal Cord Independence Measure (SCIM)*** | The SCIM assesses self-care management, respiration and sphincter management, and functional mobility after a SCI. With excellent interrater reliability (r = 0.90),^110^ the SCIM is reported to be more sensitive to functional changes than the FIM.^111^ | ICF domain = Activity |
| ***Numerical Pain Rating Scale (NPRS)*** | Pain is a significant problem in many individuals with SCI. A 0–10 Point Numerical Pain Rating Scale (NRS) is recommended as the outcome measure for pain intensity after SCI^112^ during acute and subacute phases. Pain severity can be categorized into 3 distinct groups as relates to pain interference: 1-3 (mild), 4-7 (moderate), 8-10 (severe)^113^ | ICF domain = Body Structure & Function |
| ****Fatigue Severity Scale (FSS)*** | The Fatigue Severity Scale (FSS) is may be the most widely used measure of fatigue in neurologic disorders^114^ and is a unidimensional measure that measures the effects of fatigue on function. The FSS is easy to use both in clinical practice and research, quick to administer, and its focus on the effects of fatigue on function makes its use in rehabilitation settings particularly appealing.^115^ The FSS has acceptable reliability with regard to internal consistency, test-retest reliability, and validity in persons with SCI.^115^ | ICF domain = Body Structure & Function |
| ***Penn Spasm Frequency Scale (PSFS)*** | The PSFS is a self-report measure to assess a patient’s perception of spasticity frequency and severity following a SCI. With excellent internal consistency (ICC = 0.90),^116^ the current version was modified from the original to include both frequency and severity.^117^ | ICF domain = Body Structure & Function |
| ****Patient Health Questionnaire - 9 (PHQ-9)*** | The PHQ-9 is a self-report measure to assess the presence and intensity of depressive symptoms. For SCI, the PHQ-9 demonstrates excellent internal consistency (Chronbach’s alpha = 0.87)^118^ and construct validity (r = 0.78).^119^ | ICF domain = Body Structure & Function |
| ***General Anxiety Disorder - 7 (GAD - 7)*** | The GAD-7 is a self-report measure to assess severity of anxiety symptom over the past two weeks. When compared with SCI-QOL Anxiety, a correlation of 0.67 and reliability of 0.85 for the GAD-7 provides some support of its use after SCI.^120^ | ICF domain = Body Structure & Function |
| ***International SCI Quality of Life Basic Data Set*** | The ISCIQOL Basic Data Set is a three-item quality of life questionnaire suitable for SCI populations containing 3 variables rating satisfaction with general quality of life, physical health, and psychological health.^121^ Items are answered on a 10-point likert scale that ranges from 0 (completely dissatisfied), to 10 (completely satisfied). | ICF domain = Participation |
| ***Qualitative Questionnaire*** | Participants will be asked questions regarding their experience during the invention such as their likes and dislikes; notable changes or observations; and overall satisfaction with their care. | ICF domain = Participation |
| **Aim 3 Outcomes:** To describe the intensity of RGT and UC gait training | | |
| ****Heart Rate (HR)*** | **Polar heart** **rate monitor** (RS300X, Polar®) will provide data on the day, duration, and intensity (average and maximum) of gait training sessions for both RGT and UC. Participants will be provided a Polar heart rate monitor to wear during each gait training session for the entire length of the study, and gait training session data will be collected weekly. These monitors record beat to beat heart rates and store up to 16 sessions of heart rate data. Each week study staff will upload participants’ heart rate data using Polar’s FlowLink technology via the Polarpersonaltrainer.com website. | ICF domain = Body Structure & Function |
| ****Ratings of Perceived Exertion (RPE)*** | The Borg RPE is a 15-point scale with verbal descriptors to standardize perceived exertion across tasks and individuals. Participants will be asked to provide a self-reported intensity level on the Borg Rating of Perceived Exertion Scale^122^ during RGT and UC gait training sessions. A self-report of 12 to 14 on the RPE indicates moderate intensity. The Borg RPE scale has been shown to be a valid measure of exercise intensity with weighted mean validity coefficient of 0.62 for HR.^123^ | ICF domain = Body Structure & Function |
| ***Number of Steps*** | The Ekso device records several data points for each session including **number of steps**, “Up” time (the amount of time spent standing in the device), “Walk” time (the amount of time spent walking in the device), and device assistance scores. While all of these data values will be recorded to describe each RGT session and tracked to monitor progression of the RGT intervention, the number of steps per session will be utilized as an indicator of RGT session intensity.^42,91^ We will consult our Consumer Advocates for recommendations on incorporating device scores such as “Up” time and “Walk” time as additional measures of intensity.  Number of steps for the UC group will be collected via pedometer during each gait training session. The number of steps captured on the device will be recorded on the CRF after each gait training session. The watch will be reset before each use. | ICF domain = Activity |
| *Each of these measures are core and supplemental instruments of the SCI CDE as developed through the collaboration of the International Spinal Cord Society, the American Spinal Injury Association, and the National Institute of Neurological Disorders and Stroke CDE team, and referenced at http://www.commondataelements.ninds.nih.gov/SCI.aspx. | | |

